##### Intelligence quotient

Total IQ is estimated using five subtests of the Wechsler Intelligence Scale for Children (WISC-III) [50]: Vocabulary, Similarities, Block Patterns, Picture Completion and Digit Span. These subtests are known to correlate between .90–.95 with the Full Scale IQ [51].

##### Demographics

Ethnicity, family-structure and SES (composite measure based on the average of highest level of completed education of both parents and the family income) are recorded via single questions that parents fill out online.

##### Parental psychopathology

Parental psychopathology is measured using the General Health Questionnaire (12 items) (GHQ-12) [52] and the ADHD rating scale (46 items) [53], for identifying minor psychiatric disorders and ADHD in the general population, respectively. The English version of the GHQ-12 shows good internal consistency with an average Cronbach’s α of .90. Also, construct validity has been confirmed. Answers range from 0 (*never*) to 4 (*often*) with higher scores reflecting more symptoms of psychiatric disorders. The English version of the ADHD Rating Scale is a highly reliable questionnaire with adequate criterion-related validity [53]. Parents fill out 23 items concerning behavior in the last 6 months and 23 items concerning childhood behavior. Answers are scored on a 4-point scale ranging from 0 (*never*) to 3 (*very often*) with higher scores reflecting more ADHD symptoms.

#### Measurements CAU

In order to make participation in the CAU group less burdensome and thereby enhancing inclusion of CAU participants, there will be no blood collection by venipuncture. In addition, parents and teachers have to fill out fewer questionnaires compared with parents and teachers of children in the dietary treatment arm. Parents do not have to fill out the BRIEF, CarerQol, Family Functioning Questionnaire and the Brief Scale of Parental Behavior. Teachers do not have to fill out the BRIEF and CSBQ.

### Sample size and power

The justification of sample size is calculated based on the assumption of superiority: we assume that the ED is more effective than the healthy diet on the ordinal primary outcome respondership (i.e. five categories: full responder, partial responder, mixed responder, non-responder and deterioration). A clinically relevant outcome is defined as detecting twice as many full responders in the ED group than in the healthy diet group. Each dietary group includes 81 children. With this sample size and using ordinal regression, the power is 0.99 (α = 0.05, two sided test) to detect double the amount of full responders in the ED compared with the HD (Table 4: scenario 1). In addition, the power to detect one and a half times as many full responders in the ED compared with the healthy diet is 0.64 (α = 0.05, two sided test) (Table 4: scenario 2).

**Table 4 Tab4:** Hypothetical Distribution of Participants for Power Calculation

	Full responder	Partial responder	Mixed responder	Non-responder	Deterioration
Scenario 1					
Elimination diet	16 (20)	45 (55)	10 (12%)	6 (8%)	4 (5%)
Healthy diet	8 (10%)	24 (30%)	21 (25%)	16 (20%)	12 (15%)
Scenario 2					
Elimination diet	12 (15%)	37 (45%)	13 (16%)	11 (14%)	8 (10%)
Healthy diet	8 (10%)	24 (30%)	21 (25%)	16 (20%)	12 (15%)

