### Study design

#### Randomization

Originally, the TRACE study was a three arm randomized controlled trial: participants were randomized to an elimination diet, healthy diet or CAU. However, randomization across a dietary intervention versus CAU proved not feasible. Parents usually had a strong preference towards either a dietary intervention or CAU. This resulted in an extremely slow inclusion rate, a high number of drop-outs and thereby unrepresentative groups of CAU. Therefore, after inclusion of 17 participants, the design was changed into a two arm randomized controlled trial (elimination diet vs. healthy diet) with a non-randomized comparator arm (CAU). Participants interested in a dietary intervention are randomized (50:50) to either an ED or a healthy diet with randomization within each participating center. Randomization by means of minimization is performed, including sex and age as factors, resulting in four groups. Within each group, blocked randomization is used (block size eight). The non-randomized comparator arm includes children who are being treated with CAU. Researchers disclose the group allocation to parents via a sealed envelope. Participants, researchers and dieticians are aware of treatment allocation. Researchers who will code the behavior observation (see secondary outcomes) are blinded to group allocation and time of assignment.

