### Statistical analyses

All primary analyses will be Intention To Treat. The primary outcome will be measured as an ordinal variable with five categories. Therefore, the effect of the intervention will be measured in terms of odds ratio, comparing odds for reducing ADHD symptoms and emotion dysregulation symptoms in the elimination diet group with the corresponding odds in the healthy diet group. Multiple logistic regression analyses will performed to compute the odds ratio and 95% confidence intervals, using ordinal logistic regression analysis. The CAU group will be used as a reference group.

Differences in continuous outcome measures between the dietary trajectories will be determined with analyses of ANCOVA. The follow-up value (T1, after five weeks) will be added as the dependent variable and the baseline value will be added as covariate. The two dietary groups will be compared on all outcomes at T1, using T0 scores as covariates. Clinical significance will be estimated using the partial eta squared effect. The CAU group will be used as a reference group.

In addition, a repeated measures ANOVA will be performed. First, the whole sample will be used (Intention to Treat) to determine whether adding a dietary treatment has beneficial outcomes on costs and effects of the whole treatment trajectory after 12 months (regardless of continuing the dietary treatment after 5 weeks or not). Next, per-protocol and post-hoc analyses will be performed using repeated measures ANOVA where the main outcome measures will be compared across the three conditions (i.e. elimination diet; healthy diet; CAU). Also, we will determine how many children adhered to the diet after 12 months, whether the intervention effects maintained after 12 months, which products are eliminated from the diet after 12 months and the nutritional quality of the attained diet after 12 months.

Finally, two moderator analyses will be performed: one comparing dietary responders versus non-responders (predicting respondership) and another comparing children/families adhering to a dietary treatment versus children/families that are not able to do so (predicting adherence). Both moderator analyses will be performed to compare children/families after 5 weeks and after 1 year of treatment.

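### The stated power of 0.99 (and 0.64) holds for the whole Table 4 shifts, not for doubling (or 1.5 times) the full responders, the effect it is attached to

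*Protocol article*

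**What the plan says.** The Sample size and power section takes the five-category ordinal respondership variable as the primary outcome. It sets the target on one category: "A clinically relevant outcome is defined as detecting twice as many full responders in the ED group" compared with the healthy diet group. The arm size follows: "Each dietary group includes 81 children". The power claim then reads "With this sample size and using ordinal regression, the power is 0.99", at two-sided 0.05, "to detect double the amount of full responders in the ED compared with the HD (Table 4: scenario 1"). The second claim has the same form: "the power to detect one and a half times as many full responders in the ED compared with the healthy diet is 0.64", with a pointer to scenario 2.

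Table 4 gives all five categories for both arms. The Statistical analyses section plans an odds ratio with a 95% confidence interval, "using ordinal logistic regression analysis".

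**The concern.** The effect named in the sentence and the effect that was powered are different. Doubling the full responders is a gain of 10 percentage points in the top category (10% to 20%). Scenario 1 contains that gain and also 25 further points in partial response (30% to 55%), while mixed response, non-response and deterioration together fall from 60% to 25%. Scenario 2 is built alike: 5 points in full response (10% to 15%), 15 in partial response (30% to 45%), and the lower three from 60% to 40%. The text gives no reason for the partial-responder gain and does not say that the power depends on it.

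This is the only sample-size justification for the primary comparison. Someone who takes the prose at face value will believe that 81 per arm is almost certain to detect a doubling of full responders, and may weigh the final result accordingly.

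**Working it through.** **Inputs.** From Sample size and power: 81 per arm (N = 162), two-sided 0.05, ordinal regression, Table 4. From Randomization: 1:1 allocation. From Statistical analyses: ordinal logistic regression, taken here as the proportional-odds model with one odds ratio. No loss to follow-up is applied, because none is stated in the sample-size text.

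**Formula.** Whitehead's approximation for the proportional-odds model with 1:1 allocation, where p̄ₖ is the mean of the two arms' proportions in category k:

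V = (N/12)(1 − Σ p̄ₖ³), power = Φ(|ln OR|·√V − 1.96)

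Each result was also checked by simulating a tie-corrected rank test, which is the proportional-odds score test (40,000 trials). Scenario 1, scenario 2 (percentages) and the odds ratio of 2.25 were further checked with a simulated proportional-odds likelihood-ratio test (1,500 trials).

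**Step 1: reproduce the stated figures.**

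Scenario 1, percentages:
- p̄ = 0.150, 0.425, 0.185, 0.140, 0.100, so Σp̄³ = 0.0902.
- V = 13.5 × 0.9098 = 12.28 and √V = 3.505.
- The fitted common odds ratio is 3.62, with ln = 1.285.
- Power = Φ(1.285 × 3.505 − 1.96) = Φ(2.55) = 0.995.
- The rank test gives 0.992 and the likelihood-ratio test 0.989. The stated 0.99 reproduces.

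Scenario 2, percentages:
- Σp̄³ = 0.0702, V = 12.55 and √V = 3.543. The fitted odds ratio is 1.91, with ln = 0.647.
- Power = Φ(0.33) = 0.63. The rank test and the likelihood-ratio test both give 0.62.
- From the printed counts, the formula gives 0.66 and the rank test 0.65. The stated 0.64 lies within the rounding of Table 4.

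**Step 2: what effect is that?** Cumulative odds ratios, elimination diet against healthy diet:

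| Cut | Scenario 1 | Odds ratio | Scenario 2 | Odds ratio |
|---|---|---|---|---|
| Full | 20% v 10% | 2.25 | 15% v 10% | 1.59 |
| Full or partial | 75% v 40% | 4.50 | 60% v 40% | 2.25 |
| Down to mixed | 87% v 65% | 3.60 | 76% v 65% | 1.71 |
| Down to non-responder | 95% v 85% | 3.35 | 90% v 85% | 1.59 |

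For example, the full-or-partial cut in scenario 1 is (0.75/0.25)/(0.40/0.60) = 4.50. The cut that represents doubling is the smallest of the four. The fitted value of about 3.6 comes from the other three.

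**Step 3: the named effect under the planned model.** Apply one odds ratio to every cut of the healthy-diet column.

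- Doubling: (0.20/0.80)/(0.10/0.90) = 2.25. The elimination-diet column becomes about 20/40/21/12/7%. Σp̄³ = 0.0637, √V = 3.555, ln 2.25 = 0.811. Power = Φ(0.811 × 3.555 − 1.96) = Φ(0.92) = 0.82. The rank test and the likelihood-ratio test both give 0.817. Independent repeats of the simulation gave 0.81.
- 1.5 times: (0.15/0.85)/(0.10/0.90) = 1.59. The column becomes about 15/36/23/15/10%. Σp̄³ = 0.0601, √V = 3.562, ln = 0.463. Power = Φ(−0.31) = 0.38. The rank test gives 0.37.

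**Step 4: where scenario 1 gets its power.** Keep full responders at 10%, raise only partial responders to 55%, and shrink the lower three in proportion. Power is then 0.73 to 0.76, depending on the method. Instead double full responders, hold partial at 30%, and shrink the lower three in proportion: 0.31 to 0.33. Most of the 0.99 therefore rests on the gain that the sentence does not mention.

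**The case against.** The strongest defence is that nothing is miscalculated and nothing is hidden. Each power statement points to its scenario, Table 4 prints every category, the outcome is named as ordinal, and a full distribution is a legitimate way to specify an ordinal alternative. All of this stands. It makes the problem one of labelling: the sentence attaches a correct number to an effect that does not generate it.

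It is also true that doubling one category leaves the other four open, so the defined effect has no single power under a five-category test. The 0.81 is the value under the planned model, not the only possible value.

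Two stronger readings are tempting.

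- A reader might infer that the trial is badly underpowered for its defined effect. Support might be sought in a direct 20% v 10% comparison (power 0.43), or in a doubling in which all other categories shrink in proportion (0.20; 0.09 for 1.5 times). The documents do not support this. The first test is not planned, and the second is a constructed alternative that lowers partial response while full response rises. Under the planned model, 0.81 is about the conventional 80%.
- A reader might infer that full response contributes almost nothing, because power stays near 0.97 with full responders unchanged at 10%. That case needs 65% partial responders, a figure found nowhere in the article. With the article's 55%, power is about 0.74.

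Nor does the article claim that a null result would exclude a doubling. The planned confidence interval would limit such a reading. That an ordinal test can be significant without a difference in the top category is true of any ordinal analysis and is no defect of this plan.

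**Conclusion.** The point holds as a misdescribed power statement and not as an arithmetic error. The 0.99 belongs to the whole scenario 1 shift (75% v 40% full or partial response, common odds ratio about 3.6). The 0.64, recomputed as about 0.62 to 0.65, belongs to the whole scenario 2 shift (60% v 40%, odds ratio about 1.9). Neither is the power for the change in full responders alone. With that change expressed as a common odds ratio, power is about 0.81 for a doubling and about 0.37 for 1.5 times. No version examined without the extra partial-responder gain reaches 0.99.

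These figures assume the healthy-diet column of Table 4, 81 analysed per arm, two-sided 0.05, no covariates and proportional odds. The sample size is not shown to be inadequate. The correction is worth making because the article rests its justification on these figures, but it does not threaten the design.

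**What to change.** Keep N = 162 and the planned analysis, and reword the Sample size and power section in three places:

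1. State that 0.99 and about 0.62 to 0.65 are conditional on the full scenario 1 and scenario 2 distributions, and name the partial-responder gains (30% to 55%, and 30% to 45%) as part of those assumptions.
2. Add the power under proportional odds: about 0.81 for a common odds ratio of 2.25 (full responders 10% to 20%) and about 0.37 for 1.59 (10% to 15%).
3. State the target effect on the ordinal scale, either as a common odds ratio or as the full Table 4 distribution. Which of the two is a matter of preference. Either one fixes all five categories, which a target on full responders alone does not.

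The change affects wording only. Its one downside is that the stated power for a doubling of full responders becomes less favourable, about 0.81 in place of 0.99.

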### Data collection and management

Participants will only be identifiable via a unique code assigned at the date of inclusion to anonymize all data. Non-anonymous data such as informed consents will be stored in password protected folders and in a locker. We use the online electronic data capture software CASTOR EDC to collect and store questionnaire data. We also enter and store data in CASTOR EDC which is collected during an assessment at a Karakter or Triversum - GGZ-NHN location, such as physical measurements, COTAPP observation form and outcomes of the IQ test. These data then are stored in a locker. Video-data of the DB-DOS and Actigraph data will be anonymously stored on a network attached storage. Only appointed researchers have access to this storage. Data collected by the dieticians, such as information collected during weekly appointments with parents, are stored in Microsoft Access. Nutritional assessments (of three days) will be stored in password protected folders. Researchers will check the data collected by dieticians bi-weekly for completeness and discuss this with the dieticians. After completion of the study, all data will be entered again manually to compare the entered data in CASTOR EDC and to check for mistakes.

Parents and teachers only can continue to a different questionnaire if all items are completed. If questionnaires are not filled out on time, researchers will remind parents and teachers first via e-mail (twice) and then via telephone. Researchers will check which problems parents and teachers encounter in order to help them to complete the questionnaires. To prevent drop-out at the last assessment after 12 months, researchers will explicitly mention the duration of the participation of 1 year during the intake. If parents refuse to attend the last assessment, researchers will check whether parents want to participate in other measurements (e.g. Actigraph, online questionnaires, food diary, stool sample) without visiting a Karakter or Triversum - GGZ-NHN location, in order to collect as much data as possible. Parents can declare their travel expenses up to 25 euros. Children will receive at T0, T1 and T4 a small gift worth five euros. At the last assessment, parents receive an extra reimbursement of 25 euros. Participants may withdraw from the study for any reason at any time.

### Statistical analyses

All primary analyses will be Intention To Treat. The primary outcome will be measured as an ordinal variable with five categories. Therefore, the effect of the intervention will be measured in terms of odds ratio, comparing odds for reducing ADHD symptoms and emotion dysregulation symptoms in the elimination diet group with the corresponding odds in the healthy diet group. Multiple logistic regression analyses will performed to compute the odds ratio and 95% confidence intervals, using ordinal logistic regression analysis. The CAU group will be used as a reference group.

Differences in continuous outcome measures between the dietary trajectories will be determined with analyses of ANCOVA. The follow-up value (T1, after five weeks) will be added as the dependent variable and the baseline value will be added as covariate. The two dietary groups will be compared on all outcomes at T1, using T0 scores as covariates. Clinical significance will be estimated using the partial eta squared effect. The CAU group will be used as a reference group.

In addition, a repeated measures ANOVA will be performed. First, the whole sample will be used (Intention to Treat) to determine whether adding a dietary treatment has beneficial outcomes on costs and effects of the whole treatment trajectory after 12 months (regardless of continuing the dietary treatment after 5 weeks or not). Next, per-protocol and post-hoc analyses will be performed using repeated measures ANOVA where the main outcome measures will be compared across the three conditions (i.e. elimination diet; healthy diet; CAU). Also, we will determine how many children adhered to the diet after 12 months, whether the intervention effects maintained after 12 months, which products are eliminated from the diet after 12 months and the nutritional quality of the attained diet after 12 months.

Finally, two moderator analyses will be performed: one comparing dietary responders versus non-responders (predicting respondership) and another comparing children/families adhering to a dietary treatment versus children/families that are not able to do so (predicting adherence). Both moderator analyses will be performed to compare children/families after 5 weeks and after 1 year of treatment.

For the cost-effectiveness analysis, all cost data will be accumulated over the 12 months period. Cost differences between the two dietary conditions and CAU will be compared. Incremental cost-effectiveness ratios will be calculated by dividing cost differences between treatments by differences in Quality Adjusted Life Years, as estimated from EQ-5D scores. Uncertainty analysis using 5000 bootstraps will be performed and cost-effectiveness planes and cost-effectiveness acceptability curves will be plotted.

The impact of missing data on the outcome measurements will be evaluated using different methods, such as Last Observation Carry Forward (LOCF) and Multiple Imputation (MI).

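### The primary ordinal model does not name centre, sex and age, the factors used to allocate the diets; adding them costs nothing and protects power if they predict response

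*Protocol article*

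**What the plan says.** On allocation, the Randomization section of the Protocol article states: "Participants interested in a dietary intervention are randomized (50:50) to either an ED or a healthy diet with randomization within each participating center". It continues: "Randomization by means of minimization is performed, including sex and age as factors, resulting in four groups". Blocks of eight are used within those groups.

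On the primary analysis, the Statistical analyses section treats respondership as a five-category ordinal variable and states: "Multiple logistic regression analyses will performed to compute the odds ratio and 95% confidence intervals, using ordinal logistic regression analysis". No covariate is listed for this model, and none is ruled out.

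On the continuous outcomes, the same section does go down to covariate level: "The two dietary groups will be compared on all outcomes at T1, using T0 scores as covariates". Centre, sex and age are not mentioned there either.

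The Sample size and power section does not mention adjustment.

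**The concern.** Allocating within centre, sex and age group forces the two diets to be nearly balanced on these factors. If a factor predicts response, that balance takes its contribution out of the chance difference between the diets. A model that omits the factor does not know this and still counts the variation as error. Its standard error is then too large for the design that was run, its type I error falls below the nominal 5%, and power is lost.

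Power is what is at stake. It matters mostly in scenario 2 (one and a half times as many full responders), where the plan starts from only 0.64. The factors are known for every child before allocation, so the loss can be avoided without new data.

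**Working it through.** **Inputs from the plan.** "Each dietary group includes 81 children" (Sample size and power); two-sided α = 0.05. Table 4 counts, from full responder to deterioration:
- healthy diet, both scenarios: 8, 24, 21, 16, 12
- elimination diet, scenario 1: 16, 45, 10, 6, 4
- elimination diet, scenario 2: 12, 37, 13, 11, 8

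**Step 1: reproduce the stated power with treatment only.** For scenario 1 the plan states that "the power is 0.99 (α = 0.05, two sided test) to detect double the amount of full responders in the ED compared with the HD"; for scenario 2 it states 0.64. Whitehead's score approximation for proportional odds uses

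- Z = (pairs in which the elimination-diet child is better − pairs in which that child is worse) / (N + 1)
- V = n₁n₂N / [3(N + 1)²] × (1 − Σ p̄³), with p̄ the pooled category proportions
- log odds ratio θ = Z / V, and power = Φ(θ√V − 1.96)

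Here n₁n₂N / [3(N + 1)²] = 81 × 81 × 162 / (3 × 163²) = 13.335.

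Scenario 1: Z = (3725 − 1274) / 163 = 15.04. Σp̄³ = 0.091, so V = 13.335 × 0.909 = 12.12. θ = 1.24 (odds ratio 3.46). Power = Φ(1.24 × 3.48 − 1.96) = Φ(2.36) = 0.991.

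Scenario 2: Z = (3185 − 1847) / 163 = 8.21. Σp̄³ = 0.071, so V = 13.335 × 0.929 = 12.39. θ = 0.663 (odds ratio 1.94). Power = Φ(0.663 × 3.52 − 1.96) = Φ(0.372) = 0.645.

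Using the Table 4 percentages in place of the counts gives 0.989 and 0.615. Simulating an unadjusted proportional-odds model (3000 trials per setting) gives 0.992 for scenario 1, and 0.652 (counts) or 0.633 (percentages) for scenario 2. The plan's figures are therefore reproduced without covariates.

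**Step 2: compare the model without and with the three factors.** The documents give no prognostic strength and no expected split for these factors, so the following are assumptions. Each factor has the same log odds ratio b. Splits are 60/40 for centre, 75/25 for sex and 50/50 for age. Each trial has 162 children, allocated in blocks of eight within centre × sex × age. The Table 4 percentages apply at the average covariate value. Tests are Wald tests at 1.96.

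| b (odds ratio per factor) | Scenario 2 power, without → with | Gain (points) | Scenario 1 power, without → with |
|---|---|---|---|
| 0 (1.0) | 0.634 → 0.635 | 0.1 | 0.992 → 0.993 |
| 0.3 (1.35) | 0.617 → 0.628 | 1.1 | not run |
| 0.5 (1.65) | 0.591 → 0.612 | 2.1 | 0.989 → 0.991 |
| 0.8 (2.2) | 0.538 → 0.596 | 5.8 | 0.983 → 0.986 |
| 1.2 (3.3) | 0.441 → 0.562 | 12.1 | 0.969 → 0.986 |

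Read each row across, not down. Both models lose power as b grows, because strong factors spread the outcome; only the difference within a row is the cost of omission. There were 3000 trials per setting for scenario 2 and 1500 for scenario 1. The simulation error of each scenario 2 figure is about 0.9 points.

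**Step 3: type I error.** Without the factors: 0.048 (b = 0), 0.052 (0.3), 0.046 to 0.050 (0.5), 0.041 to 0.042 (0.8) and 0.032 (1.2). With the factors: 0.050 to 0.059. Simulation error is 0.3 to 0.4 points. The unadjusted test is clearly conservative only when all three factors are strong. The adjusted Wald test runs slightly above 0.05 in some settings (0.057 over 6000 trials at b = 0.5), so a small part of the power gain comes from that.

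**Step 4: a second simulation.** At a true conditional odds ratio of 2.0, power without and with the factors is 0.70 and 0.71 at b = 0, 0.66 and 0.69 at b = 0.5, and 0.61 and 0.67 at b = 0.8. The pattern is the same.

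**The case against.** The strongest objection is that silence is not exclusion. The plan calls the regression *multiple*, which ordinarily implies more than one predictor. The article condenses a fuller protocol, and a covariate list may stand there or in an analysis plan that is not shown. The baseline term in the ANCOVA is part of what makes it an ANCOVA, so it does not show that the ordinal model has no covariates. Power is routinely computed without covariates, so the match in step 1 does not settle the matter. All of this stands. A reader might infer that the primary model omits the allocation factors; the document does not say so, only that it does not name them.

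The second objection is that the harm is assumed. Respondership is a category of within-child percentage change, and a factor that predicts baseline severity need not predict response. With no effect of the factors there is no loss. The larger losses need all three to have odds ratios of 2.2 or more at once. For scenario 1, the effect that the plan calls clinically relevant, power stays at or above about 0.97 either way. This stands too, and it limits the size of the point.

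The third concerns the odds ratio. A reader might infer that the unadjusted odds ratio is biased towards 1. It is not: the odds ratio is non-collapsible, so the unadjusted value is a valid marginal effect and the adjusted value a conditional one. They are different estimands.

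None of this argues against naming the factors. Adjustment costs no visible power when they are not prognostic, and the trial already holds the data.

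**Conclusion.** The point holds as a free improvement, not as a demonstrated error. The plan balances the diets on centre, sex and age, does not name these factors for the primary model, lists only the baseline value for the five-week ANCOVAs, and states power that matches treatment alone. If the analysis were run without the factors and they predicted response, it would be mildly conservative.

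The cost in scenario 2 runs from nothing to about 12 points of power. It is about 1 to 2 points under modest assumptions (odds ratio 1.35 to 1.65 per factor). In scenario 1 it is at most about 2 points. These figures rest on assumed splits, equal strength for all three factors, and blocked allocation within centre, sex and age group.

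It would be tempting to conclude that the primary test is invalid. The documents do not support that: any departure from 5% in an unadjusted test is towards too few false positives, so validity is not threatened. No gain was computed for the ANCOVAs; the case there is only consistency with the design.

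**What to change.** Fit the primary elimination diet versus healthy diet ordinal logistic model with diet plus centre, sex and age group, as used in allocation, as fixed covariates. Report the diet odds ratio and 95% CI from that model, and label it as conditional on these factors. Add the same terms to the five-week ANCOVAs alongside the baseline value.

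The cost is one or two sentences of analysis wording. It needs no new data and no change in sample size. Written down before the results are seen, it also fixes the covariate set. If the full protocol or analysis plan already lists these covariates, nothing more is needed than to confirm it.
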